### Power calculation

2.12

The STHLM0 and STHLM0+ combined have >200 000 men in the eligible age group between 2007 and 2023 [22]. Considering life expectancy of 11.5 yr on average for men aged 75–79 yr and 10 yr for men aged 80 yr, we can assume that, with a minimum of 200 000 men eligible for the study and 12 500 men enrolled each year, around 35 000 deaths would be recorded during the follow-up from 2007 to 2023. Hence, assuming a baseline cumulative mortality of 0.80 after 17 yr and a proportion of screening of 20%, Table 1 summarizes the power according to five different scenarios of potential reduction in mortality. Based on the power calculations, the study is powered sufficiently (>90%) to detect a benefit of at least 1.5% absolute mortality reduction. A minimum of 1.28% absolute risk reduction is necessary to guarantee at least 80% power.

**Table 1 t0005:** Power calculations for all-cause mortality

ARR (%)	HR^a^	Power with 35 000 deaths (%)	Minimum deaths needed for 80% power
1.0	0.970	62.5	∼52 700
1.5	0.956	92.0	∼24 200
2.0	0.941	99.6	∼12 800
2.5	0.927	>99.9	∼8500
3.0	0.913	>99.9	∼5930

ARR = absolute risk reduction; HR = hazard ratio.

a Hazard ratios are approximates based on the baseline mortality and the absolute reductions.

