## Introduction

1

Prostate cancer (PCa) screening allows for the early detection of potentially aggressive PCa cases to reduce mortality and morbidity [1]. Among Swedish men, PCa is the leading cause of cancer mortality, accounting for nearly fifth of all cancer deaths [2]. Currently, prostate-specific antigen (PSA)-based screening is available for men with life expectancy of ≥10 yr, provided that they understand the risks and benefits of PCa screening through a shared decision-making process [3]. Current European Association of Urology and American Urology Association guidelines suggest PSA-based screening up to ages 70 or 74 yr [3,4]. Despite these recommendations, PSA-based screening in men aged ≥75 yr is common [[5], [6], [7]]. As populations live longer [8], the number of older men with at least ≥10 yr of life expectancy is increasing. In 2024, Swedish men aged 75 yr had average life expectancy of 12.44 yr, while those aged 79 yr had average life expectancy of 9.74 yr [9]. With this trend, life expectancy might exceed 10 yr in men older than 79 yr in the near future. Therefore, fit men aged ≥75 yr could be considered for screening according to medical guidelines.

On the contrary, with increasing age, the number and complexity of chronic diseases increase [10]. Septuagenarians have heterogeneous health status declining with increased age [11]. Detection of PCa that is unlikely to metastasize or cause health issues might lead to unnecessary stress or worry, with health outcomes exacerbated negatively by the potential overtreatment [12]. Furthermore, if a PCa case is to be detected, the choice of radical or conservative therapy can have an impact on survival [[13], [14], [15]].

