### Main analysis—sequential design with the CSW approach based on age at enrollment

2.5

Emulated target trials assign men into one of the two screening arms based on their screening pattern during the eligibility period, which starts when they attain the age of interest for the study (75–79 yr) for the first time and every month thereafter (eg, at age 75 yr, 75.083 yr, 75.167 yr, and so on).

Screening is ascertained within the 1st month from trial initiation, representing the eligibility and assignment period. Eligible men with at least one PSA test in this period will be assigned to the screening arm. Those with no PSA test in this window will be assigned to the control arm. Assignment ascertainment is assumed to be accurate for all participants, as the STHLM0 contains the data on PSA testing for men living in Stockholm and who were tested in Stockholm since 2007 [22]. Considering the assumptions of causal inference frameworks [19], the following three principles are assumed to be fulfilled:1.Positivity: Every man living in Stockholm within the age group of interest has a nonzero chance of deviating from the protocol at any point during the assessment period, and every eligible man is assumed to have had the opportunity to undergo a PSA test.2.Consistency: The survival outcome we observe for the men under the given screening strategy is the same as the outcome that would have occurred if we had explicitly assigned these patients to follow the same strategy (ie, their potential outcome). As such, the screening protocol is assumed to have been defined clearly and applied consistently throughout the study period in our study. Moreover, we assume that the statistical models used in the analysis (described below) are specified correctly.3.Exchangeability: There are no unmeasured confounders; all factors that influence both the screening assignment and the likelihood of deviating from the protocol have been measured. We assume based on the confounders accounted for in the study (described below) that we address the potential factors that impact the screening assignment.

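### The power statement rests on inputs that conflict and on a single 20/80 comparison that is not the planned analysis, so power above 90% at a 1.5% risk reduction is unsupported, though not shown to be overstated

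*Protocol article*

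**What the plan says.** Section 2.12 of the protocol article starts "with a minimum of 200 000 men eligible for the study" and "12 500 men enrolled each year". It takes life expectancy as 11.5 years on average at ages 75–79 and 10 years at age 80, and concludes that "around 35 000 deaths would be recorded during the follow-up from 2007 to 2023". Table 1 then gives power for all-cause mortality, "assuming a baseline cumulative mortality of 0.80" after 17 years and "a proportion of screening of 20" per cent. The two headline results are more than 90% power for an ARR of at least 1.5% (HR 0.956, 92.0% in Table 1), and: "A minimum of 1.28% absolute risk reduction is necessary to guarantee at least 80% power".

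Elsewhere the article states:

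- Introduction: Swedish men aged 79 had "average life expectancy of 9.74" years in 2024, and those aged 75 had 12.44 years.
- Section 2.5: "Screening is ascertained within the 1st month from trial initiation". A new trial starts every month from age 75.
- Sections 2.10.2 and 2.10.4: the monthly trials are appended, weighted by the product of a screening weight and a censoring weight, and analysed with a variance clustered by man.
- Section 2.9: the contrast is an observational analogue of intention-to-screen.

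**The concern.** Two separate problems arise.

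First, the death count sets the information in Table 1 and the 0.80 converts each ARR to a hazard ratio. If they cannot describe the same cohort, the table mixes two populations.

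Second, a fixed 20/80 split with each death counted once is not the analysis in sections 2.5 to 2.10. That analysis has a much smaller screened share in each trial, repeats the same men across trials, weights every record and lets controls be tested later.

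Section 3.1 says that failure to show a benefit should lead guidelines to consider strengthening the advice against screening after age 74. A reader of a null result would look to this section to judge how informative the null is.

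**Working it through.** **1. Reproducing Table 1.** The significance level is not stated; two-sided 0.05 is assumed because it reproduces the table. The formulas are

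- HR = ln(0.20 + ARR) / ln(0.20)
- power = Φ(|ln HR| × √(D × 0.20 × 0.80) − 1.96), with D = 35 000, so √5600 = 74.83
- deaths for 80% power = (1.96 + 0.8416)² / (0.16 × (ln HR)²)

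| ARR | Printed HR | Power, printed / recomputed | Deaths for 80%, printed / recomputed |
|---|---|---|---|
| 1.0% | 0.970 | 62.5% / 62.5% | 52 700 / 52 900 |
| 1.5% | 0.956 | 92.0% / 92.0% | 24 200 / 24 200 |
| 2.0% | 0.941 | 99.6% / 99.5% | 12 800 / 13 300 (13 200 with unrounded HR) |
| 2.5% | 0.927 | >99.9% / >99.9% | 8500 / 8500 |
| 3.0% | 0.913 | >99.9% / >99.9% | 5930 / 5900 |

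Table 1 is therefore a Schoenfeld calculation for one 20/80 comparison. At HR 0.956 a one-sided test would give 95.8% and a 1:1 split 98.8%; neither matches. Only the deaths in the 2.0% row are off, by about 3%.

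**2. The 80% threshold.** 80% power needs |ln HR| = 2.8016 / 74.83 = 0.0374, so HR = 0.9633 and ARR = 0.20^0.9633 − 0.20 = 1.22%. At ARR 1.28%, HR = ln(0.2128)/ln(0.20) = 0.961 and power is 83.7%.

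**3. Deaths implied by the other inputs.** With even entry of 12 500 men a year for T years and a constant hazard λ, deaths = 12 500 × (T − (1 − e^(−λT))/λ). A mortality of 0.80 at 17 years gives λ = −ln(0.20)/17 = 0.0947.

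- T = 16 (12 500 × 16 = 200 000 men): 97 000 deaths
- T = 17 (212 500 men): 106 900 deaths

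A hazard that rises with age is more realistic and gives fewer deaths. Using Gompertz hazards (an assumption) and entry over 17 years:

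- Fitted to 0.80 at 17 years, slope 0.08 to 0.12, 200 000 men: 73 500 to 82 500
- Fitted to life expectancy 11.5 years, same slopes and men: 72 600 to 77 300
- Fitted to life expectancy 12.44 years, same slopes and men: 64 900 to 70 500
- Fitted jointly to 12.44 years at 75 and 9.74 years at 79, 12 500 men a year: 68 400 (entry at 75), 80 800 (at 77), 94 000 (at 79)

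Conversely, under a constant hazard 35 000 deaths imply 34% dead at 17 years (T = 16) or 31% (T = 17), against the stated 80%. The implied mean survival is about 40 to 46 years, against 11.5.

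**4. Life expectancy at 80.** If life expectancy is 9.74 years at 79 and 10 years at 80, and p is the chance of surviving the year between, then approximately (1 + p)/2 + 10p = 9.74. So p = 9.24/10.5 = 0.88, a 12% chance of dying in that year. A mean remaining life of 10 years corresponds to an average hazard of about 10% a year afterwards, so mortality would have to fall after 79. The joint Gompertz fit above gives 9.1 years at age 80.

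**5. The 20% and the monthly window.** If 20% were the share tested in each month, 1 − 0.80^12 = 93% would be tested each year. If it is an annual share, the monthly share is 1 − 0.80^(1/12) = 1.8%. If it is a five-year share, the monthly share is 1 − 0.80^(1/60) = 0.37%. The section does not say which.

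A simplified simulation of pooled monthly trials with variance clustered by man, scaled to 35 000 deaths, gives a standard error of the log HR of 0.0064 (20% a year) or 0.0140 (20% over five years). Table 1 uses 1/√5600 = 0.0134. Power at HR 0.956 is then above 99% or about 90%; at HR 0.970 it is above 99% or about 59%. The simulation assumes random testing, exponential survival, no weights and no dilution by later testing. It shows only that the answer depends on the missing time base.

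**6. Direction of the death-count conflict.** Keep HR 0.956 and raise deaths to 70 000: power 99.7%. Keep 35 000 deaths and lower mortality to 0.33: ARR 1.5% becomes HR = ln(0.685)/ln(0.67) = 0.945, power 98.9%.

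**The case against.** The strongest defence is that nothing here shows power to be lower than claimed. This stands. The arithmetic of Table 1 is nearly all correct on its own inputs. Reconciling deaths with mortality in either direction raises power at ARR 1.5%. The 1.28% errs on the cautious side, and the 3% gap in the 2.0% row is in a figure marked approximate. In a fixed register cohort the power figure sets no sample size, stopping rule or analysis, and a null result would mainly be read from the differences in cumulative incidence and their precision.

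A reader might go further and infer that the design really has much less than 90% power, because few men are tested in any month and controls are tested later. The documents do not support that. Power computed for one monthly trial is not the power of the pooled analysis, where each man and each death enter many trials. Shrinking the hazard ratio for later testing while keeping Table 1's information applies a correction to a quantity the design does not have, and leaves out the larger death count. Because section 2.9 defines an intention-to-screen contrast, the tabulated ARR can also be read as already net of later testing, in which case shrinking it counts dilution twice. Section 3.2 acknowledges that opportunistic testing dilutes the benefit, but section 2.12 does not say which reading applies.

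The defence does not remove the input conflicts or the mismatch with the planned analysis.

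**Conclusion.** The claim of more than 90% power at ARR 1.5% is unsupported for the planned analysis. It is not shown to be overstated.

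- **Death count:** 35 000 is too low for the other inputs by a factor of about 1.9 (65 000/35 000) to 3.1 (107 000/35 000). This range rests on even entry and on the hazard shape; every shape tried gives the same direction.
- **Life expectancy:** 10 years at 80 contradicts 9.74 years at 79 unless mortality falls with age. An earlier calendar period does not help, because the Introduction describes life expectancy as rising and treats 10 years beyond age 79 as a future prospect. The numerical effect is small.
- **Threshold:** 1.22% on the table's own formula, not 1.28%. This and the 2.0% row are minor.
- **Design mismatch:** this is the only element that could threaten the headline figure. Its direction and size cannot be determined without the time base of the 20%, the weight variability and the meaning of the ARR.

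This should be fixed, but it does not undermine the design.

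**What to change.** In section 2.12:

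1. Make the death count and the 17-year cumulative mortality agree, preferably by taking total men and total deaths from the register, without outcome by arm.
2. Reconcile the life expectancy at 80 with the Introduction. Correct 1.28% (1.22% on the present formula) and the deaths in the 2.0% row.
3. State the significance level, the time base of the 20%, and whether the ARR is net of later testing among controls.
4. Replace Table 1 with power or expected precision for the pooled, weighted analysis clustered by man, using the monthly testing proportion from the register. Alternatively, label Table 1 a single-comparison approximation and withdraw the >90% claim until that work is done.

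Items 1 to 3 need register totals and a rewritten paragraph. The full version of item 4 takes a few days of simulation. No change to design, data or analysis is needed.

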### Hypothesis

2.1

Our hypothesis is that men aged 75–79 yr who are screened for PCa using PSA, despite no prior PCa diagnosis, gain a modest survival benefit by reducing PCa mortality through the detection and future treatment of lesions with metastatic potential.

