### Potential findings and clinical implications

3.1

The findings of this study could demonstrate the benefit of PSA-based screening among men aged 75–79 yr, no observed benefit, or increased harm. In the scenario that the study shows a modest benefit, the medical guidelines can be informed about the emerging evidence to contrast it with their current recommendations. The screening age could then be increased to include men aged 75–79 yr on the conditions that the country has high life expectancy within this age group and the patient is not frail. Moreover, the study would provide foundational support to the conduct of a screening RCT aimed at this age group. It also poses questions on how men should be assessed for their health status before providing screening diagnostics [28,29], how to ensure that the PCa screening minimizes overdiagnosis [30], how to reduce overtreatment, and which treatment modality would optimize their survival and recovery after treatment [31]. On the contrary, if the study fails to show a benefit despite the long-term follow-up, or shows increased harm, the medical guidelines should then consider strengthening the recommendation about no screening after the age of 74 yr, and the importance of urologists’ re-engagement and communication with the patients in the shared decision-making session.

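### Power is called sufficient for all-cause mortality only, where a modest effect confined to prostate cancer (PCa) death would be nearly invisible, and the Discussion attaches no precision condition to a null result

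*Protocol article*

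**What the plan says.** The Hypothesis section (2.1) expects that screened men "gain a modest survival benefit by reducing PCa mortality". Outcomes (2.8) lists all-cause mortality first and PCa-specific mortality second, and Survival analysis (2.10.4) plans differences in cumulative incidence functions (CIFs) for both at 5, 10 and 15 years.

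The Power calculation section (2.12) covers only the first. Table 1 is titled "Power calculations for all-cause mortality". It rests on the expectation that "around 35 000 deaths would be recorded during the follow-up from 2007 to 2023", a 17-year baseline mortality of 0.80 and 20% screened. It concludes that power is sufficient, above 90%, "to detect a benefit of at least 1.5% absolute mortality reduction" and puts the 80% threshold at an absolute risk reduction (ARR) of 1.28%. The five ARRs, 1.0% to 3.0%, are not derived from any assumed effect on PCa death.

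Potential findings and clinical implications (3.1) says that "if the study fails to show a benefit despite the long-term follow-up, or shows increased harm", guidelines should consider firmer advice against screening after 74. It names no outcome and sets no condition on the width of the confidence interval.

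**The concern.** The power claim and the hypothesis concern different quantities. If screening works only by averting PCa deaths, its effect on all-cause mortality is diluted by every death from another cause. The statement that the study is sufficiently powered then says little about the effect it was designed to find.

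This matters for interpretation in both directions. A null all-cause result could be the expected outcome even if screening lowers PCa mortality, yet nothing in the Discussion stops it being read as evidence of no benefit. An all-cause difference of the size in Table 1 could equally come from slight residual differences in health between tested and untested men.

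**Working it through.** **Inputs from the article.** 35 000 deaths; 20% screened; baseline mortality 0.80, so survival of 0.20, at 17 years. Alpha is not stated; two-sided 0.05 reproduces Table 1, while one-sided 0.05 does not (73.7% against the stated 62.5% at HR 0.970).

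**Reproducing Table 1.** HR = ln(0.20 + ARR)/ln(0.20). Power = Φ(|ln HR| × √(D × 0.2 × 0.8) − 1.96). With D = 35 000, √5600 = 74.83.
- HR 0.956: 0.0450 × 74.83 − 1.96 = 1.41, power 92.0% (stated 92.0%).
- HR 0.970: 62.5% (stated 62.5%).
- HR 0.941: 99.5% (stated 99.6%).
- The last two rows also agree, at over 99.9%.

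The deaths needed for 80% power agree closely. The largest gap is the 2.0% row: 13 265 at the rounded HR or 13 164 at the unrounded one, against 12 800. The 80% threshold computes to an ARR of 1.22% rather than 1.28%. Neither difference is material.

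**Assumption not in the article.** The Introduction gives PCa's share of cancer deaths only ("accounting for nearly fifth of all cancer deaths"), for Swedish men generally. The share s of all deaths in this cohort is not given; I take 3% to 10%.

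**Linking the hypothesis to all-cause mortality.** With other-cause hazard unchanged, all-cause HR ≈ 1 − s × (1 − HR for PCa), and expected PCa deaths are 35 000 × s. The same power formula applies to each endpoint.

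| s | PCa deaths | PCa HR | All-cause HR | ARR at 17 yr | All-cause power | PCa-specific power |
|---|---|---|---|---|---|---|
| 3% | 1050 | 0.90 | 0.997 | 0.10% | 4% | 28% |
| 3% | 1050 | 0.80 | 0.994 | 0.19% | 7% | 82% |
| 3% | 1050 | 0.70 | 0.991 | 0.29% | 10% | >99% |
| 5% | 1750 | 0.90 | 0.995 | 0.16% | 6% | 42% |
| 5% | 1750 | 0.80 | 0.990 | 0.32% | 11% | 96% |
| 5% | 1750 | 0.70 | 0.985 | 0.49% | 20% | >99% |
| 10% | 3500 | 0.90 | 0.990 | 0.32% | 11% | 70% |
| 10% | 3500 | 0.80 | 0.980 | 0.65% | 33% | >99% |
| 10% | 3500 | 0.70 | 0.970 | 0.99% | 63% | >99% |

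Every ARR in this grid is below the smallest row of Table 1. The formula counts rejections in the direction of benefit only, so its floor is 2.5%.

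**What the stated threshold would require.** ARR 1.28% gives HR = ln(0.2128)/ln(0.20) = 0.961. The PCa hazard would have to fall by 0.0385/0.05 = 77% at a 5% share, or 0.0385/0.10 = 39% at a 10% share. At 3% the requirement exceeds 100%.

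**The opposite error.** A hypothetical residual bias of HR 0.96, with no screening effect, gives 0.20^0.96 − 0.20 = 0.0133. That is 1.3 percentage points at 17 years, about the size the article treats as detectable. By the same formula it would be declared significant 86% of the time.

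**The case against.** Using all-cause mortality is a reasoned choice. Potential strengths and limitations (3.3) explains that cause-of-death coding worsens with age and that sticky-diagnosis bias can distort PCa mortality but not all-cause mortality. This stands: the all-cause analysis should stay. It does not show that the all-cause analysis can detect the hypothesised effect.

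A reader might infer that the Discussion sets a decision rule under which a non-significant all-cause result means no benefit. The text does not support that. It is discussion, it asks guidelines only to consider a change, and it names no outcome. Both outcomes are analysed, and PCa-specific power may be good at HR 0.80. The criticism that remains is narrower: the null reading carries no outcome, no smallest worthwhile benefit and no inconclusive category.

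A reader might also infer that Table 1 is miscalculated, or that the study as a whole is underpowered. Neither follows. The table reproduces, and PCa-specific power at HR 0.90 is uncertain (28–70%) rather than shown to be inadequate.

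On bias, the article concedes residual confounding and plans an array analysis and comparisons with younger men. HR 0.96 is illustrative, not an estimate. The array analysis works from assumed confounder values, and the younger-age contrast is aimed at death-certificate error. A non-PCa contrast is therefore a useful addition; its absence is not an error.

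**Conclusion.** The point holds in this form. The sufficiency claim is true for all-cause reductions of the size tabulated, but those sizes are not linked to the hypothesised mechanism. For PCa hazard reductions of 10–20%, all-cause power is about 4–33% across assumed PCa shares of 3–10%. Only the most favourable corner examined (10% share, PCa HR 0.70) reaches 63%.

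The results rest on three assumptions: the PCa share, an unchanged other-cause hazard, and the article's own 35 000 deaths and 20% screened. Weighting, one-month assignment windows and repeated entry of the same men could lower the effective information for both endpoints. The consequence is for interpretation, not conduct, because the register fixes the sample.

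**What to change.** 1. **Power calculation.** Limit the sufficiency statement to all-cause reductions of the stated size. Add expected PCa deaths, and power or expected confidence-interval width for PCa-specific mortality, over a stated range of PCa shares. Say that all-cause mortality is not powered for a modest effect confined to PCa death.
2. **Potential findings and clinical implications.** Conclude no benefit only if the 95% confidence interval for the difference in PCa-mortality CIFs, at a time point fixed in advance, excludes a pre-stated smallest worthwhile benefit. Otherwise call the result inconclusive.
3. **Survival analysis (a cheap addition).** Report the standardized CIF difference for non-PCa death with its confidence interval. Lower non-PCa mortality in the screened arm would point to residual healthy-screenee bias. Read it alongside the misclassification the article acknowledges, since sticky diagnosis moves deaths from other causes to PCa among screened men and would look similar.

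The cost is some wording and one more outcome from the same models. The stated power becomes less favourable, and the study may have to report an inconclusive result.
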